##### Tobacco use

Two questions will be asked about the use of tobacco products.

Heath status and tobacco use questions are integrated into the screening of alcohol use so as to reduce possible stigma of reporting alcohol use.

This questionnaire will be administered at baseline, 6 and 12 months follow-up visits. All questionnaires will be administered in English or Tswana, the two languages predominantly spoken by nearly all clinic patients.

### Sample size calculation

The sample size was calculated using the Protocol Support Tool for Randomize Control Trial Research Software (PST Version 1), for a two arm randomized controlled trial, with 80% power, significance level of 5%, two sided-tests, standard deviation of the control group measurement of 5, and a mean difference between intervention and control of 2. The minimum sample size of each group is 99. To accommodate a drop-out rate of 15% at each follow up, the sample size for each group has been increased to 140, this makes 280 in total.

### Data analysis

Means, standard deviations, and percentages will be used for descriptive statistics. *T*-test for continuous data and chi-square for categorical data will be used to examine differences between groups. Generalized Linear Model Repeated Measures 2 × 3 Analysis of Variance (ANOVA) will be used for comparing observations (alcohol use score) across the three contact periods to demonstrate a treatment intervention × time interaction. Observations with a single follow-up point missing (at either 6 or 12 months) will be imputed with the available follow-up. Data for participants who are lost to follow-up at both 6 and 12 months will be imputed using baseline values. SPSS for Windows version 17.0 (SPSS, Inc., Chicago, IL) will be used for calculations.

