### Objectives

1. To measure the prevalence of alcohol consumption amongst out-patients at [name] Hospital.

2. To describe drinking patterns of out-patients at [name] Hospital, and identify medium risk drinkers needing intervention.

3. To compare level of alcohol consumption amongst medium risk drinkers between pre-intervention, 6 months, and 12 months after intervention among out-patients at [name] Hospital.

4. To compare alcohol consumption between intervention and control groups at 6 and 12 months.

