#### Study hypotheses

• Out-patient medium risk drinkers in the intervention group reduce drinking much more than those in the control group.

• The drinking patterns of patients in the intervention group will continuously reduce over a 12 month assessment period.

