##### Alcohol consumption

The 10-item Alcohol Disorder Identification Test (AUDIT) [16] assesses alcohol consumption level (3 items), symptoms of alcohol dependence (3 items), and problems associated with alcohol use (4 items). Responses to items on the AUDIT are rated on a 4-point Likert scale from 0 to 4, with a maximum score of 40 points. AUDIT scores higher than 19 indicate more severe levels of risk; scores of 8-19 in men and 7-19 in women indicate a tendency to problematic drinking. To comply with the timeline of this study, all subjects will be asked for their alcohol consumption in the previous 6 months rather than 1 year.

The primary outcome measure used in this study is the change in drinks per week from baseline to follow-up, as estimated from the first two AUDIT questions. A secondary measure is the frequency of consuming four or more drinks per occasion (AUDIT question 3). The percentage of patients whose weekly consumption decreases, increases, or remains the same, as well as changes in a combination of the first three AUDIT item scores called the Drinkers' index, will also be evaluated in order to estimate the amount of alcohol risk reduction.

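### The one named efficacy model uses an undefined score and rests on a two-degree-of-freedom arm × time interaction, not on a stated, baseline-adjusted between-arm difference in drinks per week

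*Protocol article*

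**What the plan says.** - **Primary outcome** (Outcome measures, Alcohol consumption): "the change in drinks per week from baseline to follow-up, as estimated from the first two AUDIT questions". The same section lists other alcohol measures, among them that "changes in a combination of the first three AUDIT item scores called the Drinkers' index, will also be evaluated", and describes the full AUDIT with a maximum of 40 points.
- **Model** (Data analysis): a 2 × 3 repeated-measures ANOVA. Its stated purpose is "comparing observations (alcohol use score) across the three contact periods to demonstrate a treatment intervention" by time interaction. With three contact periods, baseline is one of the repeated outcome levels. The term *alcohol use score* appears nowhere else in the article.
- **Other tests** (Data analysis): a *t*-test "for continuous data and chi-square for categorical data will be used to examine differences between groups". No variable or visit is attached to it. Means and standard deviations are planned as descriptive statistics.
- **What the comparison is meant to answer:** Objective 4 is "To compare alcohol consumption between intervention and control groups at 6 and 12 months". The first study hypothesis is directional: "Out-patient medium risk drinkers in the intervention group reduce drinking much more than those in the control group".
- **Sizing** (Sample size calculation): a two-arm comparison with mean difference 2, SD 5, 5% two-sided and 80% power gives 99 per group, raised to 140 for drop-out.

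**The concern.** Two links are missing between the question and the analysis.

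1. **The variable.** The primary outcome is in drinks per week, but the model is for a score that the article does not define. The word score fits the Drinkers' index or the AUDIT total at least as well as it fits drinks per week. As written, the dependent variable of the main model could be chosen after the data are seen.

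2. **The test.** The plan seeks to demonstrate efficacy through an arm × time interaction. This is an omnibus F test with 2 degrees of freedom that rejects for any departure from parallel profiles. Objective 4 asks for arm comparisons at two visits, and the hypothesis says which arm should do better. A significant interaction gives neither by itself.

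There is also a supporting point on precision. Baseline is measured before randomisation, so the arms are equal there in expectation. Modelling it as a third outcome with free arm means does not use that fact.

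The efficacy finding also matters inside the trial: the delayed intervention is offered to controls only if the intervention proves efficacious.

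**Working it through.** **Step 1: reproduce the plan's own figure.** Inputs from Sample size calculation: difference 2, SD 5, two-sided 5%, power 80%.

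n = 2 × 5² × (1.960 + 0.842)² / 2² ≈ 98.1, rounded up to 99 per arm.

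This matches. Allowing 15% loss at each of two follow-ups gives 99/0.85² = 137.0 (138), or 99/0.70 = 141.4 (142), so 140 is consistent. The arithmetic is sound, but it belongs to a simple two-group comparison of means, not to an interaction test.

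**Step 2: what the interaction responds to.** Assumptions not in the article: the SD of 5 is in drinks per week and holds at every visit, and all pairs of visits share one correlation ρ. The F test has 2 and 2(2n − 2) = 392 degrees of freedom and non-centrality

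λ = (n/2) × Σ(d_t − d̄)² / [25(1 − ρ)],

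where d_t is the arm difference at 0, 6 and 12 months and n = 99.

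| Arm difference at 0 / 6 / 12 months | Σ(d_t − d̄)² | λ, ρ = 0.5 | Power, ρ = 0.5 | λ, ρ = 0.3 | Power, ρ = 0.3 |
|---|---|---|---|---|---|
| 0 / 2 / 2 (sustained) | 2.667 | 10.56 | 83% | 7.54 | 69% |
| 0 / 2 / 0 (vanished by 12) | 2.667 | 10.56 | 83% | 7.54 | 69% |
| 0 / 0 / 2 (late only) | 2.667 | 10.56 | 83% | 7.54 | 69% |
| 0 / −2 / −2 (opposite direction) | 2.667 | 10.56 | 83% | 7.54 | 69% |
| 0 / 1 / 2 (gradual) | 2.0 | 7.92 | 71% | 5.66 | 55% |
| 0 / −1 / +1 (mean effect zero) | 2.0 | 7.92 | 71% | 5.66 | 55% |

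The test cannot tell the first four rows apart. It also rejects often when the average follow-up effect is zero.

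**Step 3: precision.** For the arm difference at one visit:

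- change score: variance 2(1 − ρ) × 25
- ANCOVA on baseline: variance (1 − ρ²) × 25
- ratio ANCOVA / change = (1 − ρ²) / [2(1 − ρ)] = (1 + ρ)/2

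This is 0.65 at ρ = 0.3, 0.75 at 0.5 and 0.90 at 0.8. It is below 1 for every ρ below 1.

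**Step 4: power over a range of ρ.** The effect is 2 at both follow-ups, with 99 per arm. The ANCOVA column uses a single visit, with SD 5√(1 − ρ²) and a normal approximation.

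| ρ | 2 × 3 interaction | ANCOVA, one visit |
|---|---|---|
| 0.2 | 62% | 82% |
| 0.3 | 69% | 84% |
| 0.4 | 76% | 87% |
| 0.5 | 83% | 90% |
| 0.6 | 91% | 94% |
| 0.7 | 97% | 98% |
| 0.8 | above 99% | above 99% |

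The interaction reaches the planned 80% only somewhere between ρ = 0.4 and ρ = 0.5. The gap to ANCOVA is about 20 percentage points at ρ = 0.2 and has nearly gone by 0.7.

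**The case against.** A reader might infer that the planned model does not test the primary outcome at all. The article does not support that. The outcome is defined as change from baseline, and if the score is drinks per week, the arm × time interaction is exactly the joint test that this change is equal in both arms at 6 and 12 months. What is wrong is that the variable and the contrast are not fixed.

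A reader might also infer that the plan cannot say which arm drinks less. That too goes beyond the text. The same section plans means, standard deviations and *t*-tests between groups, and these could show direction and visit-specific differences. This stands in part: the output could show direction, but the *t*-test is assigned to no variable or visit, so the efficacy claim is not tied to it.

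Three further objections stand:

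- **Primary visit.** The article does not make 12 months the sole primary visit. Objective 4 names both visits, so the plan cannot be faulted for missing a 12-month target. An ANCOVA at 12 months alone would have only 5% power against an effect present only at 6 months.
- **Precision.** Keeping baseline as a repeated level is valid under randomisation and does not bias the comparison of change. The loss is one of efficiency. It depends on a correlation the article does not give, and it is small if that correlation is high.
- **Detail left to an analysis plan.** Contrasts, covariates and intervals are commonly set out there, and none is shown. Their absence alone is no finding. The mismatch between the named outcome and the modelled score, and the choice of the interaction as the demonstration of effect, are in the article itself.

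**Conclusion.** The point holds in this form. The only named model is for an undefined score, not expressly for drinks per week, and efficacy is to be demonstrated by a non-directional 2-degree-of-freedom interaction not tied to the between-arm comparison in Objective 4. Read alone, a significant result would not separate a lasting benefit from one lost by 12 months: power is 83% for either at ρ = 0.5, and 69% at ρ = 0.3.

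The precision argument is secondary. Adjusting for baseline reduces the variance of a single-visit difference to (1 + ρ)/2 of the change-score variance, a saving of 35%, 25% and 10% at ρ = 0.3, 0.5 and 0.8. These figures rest on an assumed ρ, equal correlation across visits, and SD 5 in drinks per week at every visit.

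It would be going too far to call the trial underpowered on this ground. The sample size of 99 per arm reproduces, and at ρ = 0.5 or above the interaction exceeds 80% for a sustained effect of 2.

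**What to change.** In Data analysis:

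1. Name drinks per week, estimated from the first two AUDIT questions, as the dependent variable in place of the undefined score.
2. Base the efficacy claim on the between-arm difference at 6 and 12 months from a model with baseline drinks per week as covariate, either ANCOVA or a mixed model of the two follow-ups, with 95% confidence intervals.
3. Have the sponsor state in advance whether 6 months, 12 months or the average of both is primary.
4. Keep the 2 × 3 interaction as descriptive, and say which variables and visits the *t*-tests are for.

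Sex may be added as a covariate, but this is optional. The cost is analysis wording only: the AUDIT is already administered at baseline and both follow-ups, and gender is already recorded.

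### Filling missing visits by copying the other follow-up or baseline sets about 28% of 6-to-12-month changes to zero and can bias the arm comparison in either direction

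*Protocol article*

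**What the plan says.** Under Data analysis, the protocol article states how both patterns of missing follow-up are handled. For one missing visit: "Observations with a single follow-up point missing (at either 6 or 12 months) will be imputed with the available follow-up". For two: "Data for participants who are lost to follow-up at both 6 and 12 months will be imputed using baseline values". The completed data go into a repeated-measures ANOVA "across the three contact periods to demonstrate a treatment intervention × time interaction".

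Three other statements bear on this:

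- Outcome (Alcohol consumption): "The primary outcome measure used in this study is the change in drinks per week from baseline to follow-up".
- Second hypothesis (Study hypotheses): "The drinking patterns of patients in the intervention group will continuously reduce over a 12 month assessment period".
- Expected loss (Sample size calculation): "To accommodate a drop-out rate of 15% at each follow up, the sample size for each group has been increased to 140".

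The Procedure section adds that a patient not reached at 6 months will be tried again at 12 months.

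**The concern.** Both rules put in a known number where the trial has none, and the ANOVA treats that number as a measurement.

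- **Copying one follow-up into the other** makes the 6-to-12-month change exactly zero. These patients keep a real change from baseline.
- **Copying baseline** makes the change from baseline exactly zero at both visits, which is the primary outcome itself.

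The first consequence touches the second hypothesis, which expects drinking to go on falling to 12 months. The rules write no further change into part of the data used to examine it.

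The second touches the arm comparison. Patients enter on a raised AUDIT score and the controls receive a leaflet on responsible drinking, so some fall in both arms is plausible. If so, assigning no change to wholly lost patients holds back the arm that loses more of them. Patients know their arm and only one arm is counselled, so unequal loss is possible.

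This is a rule the article states, not a detail it leaves to a fuller plan.

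**Working it through.** **Inputs from the Sample size calculation section:** difference 2, SD 5, two-sided 5%, 80% power, 99 per arm before and 140 per arm after allowance for loss, 15% loss at each follow-up.

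**The plan's own figure.** The usual two-sample formula with these inputs gives 99 per arm, as stated. Allowing for 15% loss twice, 99 / (0.85 × 0.85) = 137.02, so 138; the stated 140 is close. The sample size is not at fault.

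**Two drop-out patterns.** The article does not say whether a patient missed at 6 months is also lost at 12, so both ends are shown.

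| Share of patients | Independent misses | Permanent loss |
|---|---|---|
| Both visits missing (baseline copied) | 0.15 × 0.15 = 2.25% | 15% |
| One visit missing (other follow-up copied) | 2 × 0.15 × 0.85 = 25.5% | 0.85 × 0.15 = 12.75% |
| 6-to-12-month change set to zero | 27.75% | 27.75% |

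**Time course.** With loss unrelated to drinking, a true further fall of 2.0 is estimated as 2.0 × (1 − 0.2775) = 1.445 under either pattern. Simulation of the two rules (SD 5, correlation 0.5) gives 1.43 to 1.44.

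**12-month difference, equal loss in both arms.** In both patterns 12.75% of patients miss 12 months only and carry the 6-month effect forward; double losses carry zero. With E6 and E12 the true differences at 6 and 12 months:

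- independent: 0.85 × E12 + 0.1275 × E6
- permanent: 0.7225 × E12 + 0.1275 × E6

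| True E6, then E12 | Independent | Permanent |
|---|---|---|
| 2, 2 (constant) | 1.955 | 1.70 |
| 1, 2 (growing) | 1.83 | 1.57 |
| 3, 2 (fading) | 2.08 | 1.83 |
| 3, 0 (gone by 12 months) | 0.38 | 0.38 |

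Baseline copying shrinks the estimate. Copying a follow-up pulls the 12-month estimate towards the 6-month effect, which raises it when the effect fades. The net sign depends on both.

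**Unequal loss, no treatment effect.** If both arms truly fall by m at both visits and fractions qI (intervention) and qC (control) are lost at both visits, the expected false difference is m × (qC − qI). Type I error follows from a normal approximation with 140 per arm and a change variance in each arm of 25(1 − q) + q(1 − q)m², reading the SD of 5 as that of change. Assumed loss is 10% versus 20% per visit. This gives double losses of 10% versus 20% if permanent, and 1% versus 4% if independent.

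| Common fall m (assumed) | Permanent: false difference, type I error | Independent: false difference, type I error |
|---|---|---|
| 1 | 0.10, 5.4% | 0.03, 5.0% |
| 2 | 0.20, 6.5% | 0.06, 5.1% |
| 3 | 0.30, 8.3% | 0.09, 5.3% |
| 4 | 0.40, 10.7% | 0.12, 5.5% |
| 5 | 0.50, 13.5% | 0.15, 5.7% |

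Simulation of the full 2 × 3 interaction test agrees. For falls of 3, 4 and 5 it gives 8.7%, 11.3% and about 14.5% with permanent loss, and 5.8%, 5.4% and 5.8% with independent misses.

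**Direction.** With a true effect of 2, a control fall of 4, and 5% (intervention) versus 25% (control) lost at both visits, the estimate is 6 × 0.95 − 4 × 0.75 = 2.7. With the rates reversed it is 6 × 0.75 − 4 × 0.95 = 0.7.

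**The case against.** The strongest reply is that the harm depends on a drop-out pattern the article does not predict. Lost patients get at least six contact attempts, those missed at 6 months are tried again at 12, and the rule for one missing visit expects some to return. If misses are close to independent, few patients receive baseline values, the constant effect shrinks by about 2%, and type I error stays near 5%. This stands, and is why both ends are shown. It does not help the time course, where 27.75% holds under either pattern.

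It is also fair that a mixed model under missing at random is biased if relapsed drinkers are the ones who leave, and that assuming no change for wholly lost patients is a reasonable sensitivity analysis. Both points stand.

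Several stronger readings are tempting, but the documents do not support them:

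- **That the bias is always towards no effect when losses are equal.** The fading examples show otherwise.
- **That type I error is broken.** This needs unequal loss, a sizeable common fall and largely permanent loss together. The article gives neither the fall nor unequal rates. Selection is on total AUDIT while the outcome uses two items, so the size of any common fall is unknown.
- **That every imputed patient shows no change.** Those with one missing visit keep a real change from baseline.
- **That a primary 12-month effect is biased.** The article names no primary visit.
- **That the trial becomes underpowered.** With 140 per arm analysed, 15% double loss and SD 5, a difference of 1.70 still has 81.2% power.
- **That double losses will be counted as unchanged** in "The percentage of patients whose weekly consumption decreases, increases, or remains the same". The article does not say whether filled values enter those percentages.

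**Conclusion.** The concern holds. The copying rules are stated as final, and at the plan's own loss rate they fix 27.75% of 6-to-12-month changes at zero. A true further fall of 2.0 is then estimated as about 1.44, assuming loss unrelated to drinking. This bears directly on the second hypothesis.

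The effect on the arm comparison is real but uncertain in size. A constant effect of 2.0 is estimated at 12 months as somewhere between about 1.96 and 1.70, according to whether misses are independent or permanent. A fading effect can be overstated. The false-difference figures (type I error about 5–6% with independent misses, 5–15% with permanent loss) rest on an assumed 10% versus 20% loss and an assumed common fall of 1 to 5 units. They show that the rule cannot be defended as reliably conservative; they do not forecast this trial's error rate. Under either pattern, the copied values are analysed with no allowance for their uncertainty.

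**What to change.** In Data analysis, replace both copying rules for the primary analysis with a likelihood-based repeated-measures mixed model. It should use all observed 6- and 12-month values of drinks per week, with baseline drinks per week as covariate, arm, visit and arm-by-visit as terms, and no filled-in values. State that it assumes missing at random. The arm difference at each visit and the 6-to-12-month change within the intervention arm can then be estimated from one model.

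Keep the present rules as a labelled sensitivity analysis. If filled values were meant to enter the percentages whose consumption falls, rises or stays level, count patients lost at both visits as missing there.

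The cost is a change of wording and a little more analysis, with no new patients or data. The planned size still serves: with permanent loss, 140 × 0.85 × 0.85 = 101 per arm are seen at 12 months, giving 81.2% power for a difference of 2. The downside is reliance on missing at random, which the sensitivity analysis probes.

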#### Ethical and governance approval

We have received ethical approval from the Medunsa Research and Ethics Committee (Project number: MREC/H/220/2010:IR). [name] Hospital has also provided approval for this study.

#### Project timescales

The study will run for a period of 16 months beginning in February 2011 to June 2012.

## Abbreviations

AUDIT: Alcohol Use Disorder Identification Test; IMB: Information-Motivation-Behavioural Skills; SBI: Screening and Brief Intervention; SF-12: A 12-Item Short-Form Health Survey
